### Implementation {16c}

Enrolment will be performed by Study Secretary. Each prepared envelope will have specific number previously generated by a computer program and will be associated with the technique performed (fixation/non-fixation). The name of the technique and, therefore, assignment to intervention will be placed in the proper envelope. Surgeon will not be aware of the technique he should perform before opening the envelope.

## Assignment of interventions: blinding

### Who will be blinded {17a}

Trial participants and Study Secretary performing phone call follow-up visit will be blinded to the method used. Surgeon will be blinded for as long as possible (after the dissection, reduction of hernia sack, and creation of preperitoneal space are achieved).

### Procedure for unblinding if needed {17b}

Unblinding will take place at the end of the trial (12 months) during ambulatory visit or phone call.

## Data collection and management

### Plans for assessment and collection of outcomes {18a}

Each center designated one surgeon responsible for conducting the trial in their hospital and sent him/her to attend the meeting. Data will be collected with the use of questionnaires exclusively by members of the research team (surgeons and the Study Secretary).

### Plans to promote participant retention and complete follow-up {18b}

Patients will be encouraged to complete follow-up via talk and discussion with the surgeon. Research Team will monitor the participants to ensure follow-up completion, including email and SMS reminders. 10% of lost to follow-up is predicted.

### Data management {19}

Only study investigators will have access to trial information and dataset. Personal information about enrolled participants will be collected in closed envelope in the hospital registry. Data will be held for 20 years after the trial. To protect confidentiality, no name/surname will be used. Each participant will be assigned a code number impossible to decode without a proper list. Participants will not be identified in the resulting manuscripts or reports. The Trial Steering Committee will have access to interim results and make the final decision to terminate the trial. Interim analysis will take place in half-way of the trial.

### Confidentiality {27}

Personal information about enrolled participants will be collected in closed envelope in hospital registry. Data will be held for 20 years after the trial. To protect confidentiality, no name/surname will be used. Each participant will have a code number impossible to decode without proper list. Participants will not be identified in the resulting manuscripts or reports.

### Plans for collection, laboratory evaluation, and storage of biological specimens for genetic or molecular analysis in this trial/future use {33}

No biological specimens will be stored.

## Statistical methods

### Statistical methods for primary and secondary outcomes {20a}

All statistical calculations will be performed using the statistical suite StatSoft Inc. (2014) STATISTICA (data analysis software system) version 12.0 (www.statsoft.com) and an Excel spreadsheet. Continuous variables will be characterized by arithmetic mean, standard deviation, median, minimum and maximum (range), and 95% CI (confidence interval). Qualitative variables, on the other hand, will be presented using the frequency and percentage values (percentage). The Shapiro–Wilk W test will be used to check whether the quantitative variable came from a normally distributed population. The Leven (Brown-Forsythe) test will be used to test the hypothesis of equal variances. Significance of differences between the two groups (model of unrelated variables) will be tested by the tests of significance of differences: Student’s *t*-test (or, in the absence of homogeneity of variance, the Welch test) or the Mann–Whitney U test (if the conditions of applicability of the Student’s *t*-test are not met or for variables measured on ordinal scale). Significance of differences between more than two groups will be checked by *F* test (ANOVA) or Kruskal–Wallis test (if the conditions of ANOVA applicability are not met). If statistically significant differences between the groups are obtained, post hoc tests will be used (Tukey’s test for *F*, Dunn’s test for Kruskal–Wallis). Chi-square tests of independence will be used for categorical variables (using Yates correction for cell counts below 10, checking Cochran conditions, Fisher’s exact test, respectively). In order to determine the relationship, strength, and direction between the variables, correlation analysis will be applied by calculating the Pearson and/or Spearman correlation coefficients. *P* = 0.05 will be assumed as the significance level in all calculations.

The trial was planned as non-inferiority study with test power = 80%, *p*-value = 0.05, and threshold for clinical significance = 8%. A percentage loss of 10% was assumed. Recurrence rate was assumed to be 4% based on literature data. Based on those assumptions, minimal sample size in both arms was established at 83–102. To ensure sufficient participant numbers at completion of the trial, sample size was established at 204 participants. To maintain the integrity and clarity of our results, we chose to focus on our primary analysis. Given the focused nature of our primary research question and to maintain the power of our statistical analyses, we opted not to divide our sample further into subgroups.

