#### Secondary outcomes

Besides primary outcome secondary outcomes will also be noted.

1. Pain sensation assessed with Visual Analog Scale measured during hospital stay, 7 days post-op, 3 months, and 12 months after surgery.

2. Incidence of other complications (seroma, hematoma, infections) assessed during hospital stay, 7 days post-op, 3 months, and 12-months after surgery.

7 day post-op visit will be performed by a surgeon blinded to the arm allocation. During the visit, another form will be filled and placed in encoded envelope. Three months post-op and 1-year post-op follow-up, a phone call will be performed by the Study Secretary blinded to the allocation. Telephone call after inguinal hernia surgery is a verified and validated form of follow-up [5, 6]. If there are any concerns, the patient will be asked to attend an outpatient appointment.

Participant demographics including general medical history, body mass index, co-morbidities, age, sex, smoking status, history of hernia repairs, and family history of hernias will be noted and placed in sealed coded envelopes.

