## Assignment of interventions: allocation

### Sequence generation {16a}

Randomization will be performed with the use of the Clinical Trial Randomization Tool (National Cancer Institute) on 1:1 basis by Study Secretary. Based on randomization, 204 envelopes will be prepared, each with a unique code number. Inside, apart from blank research cards to be completed, there will also be a smaller envelope with the type of technique to be used during the procedure. Participants, the Study Secretary, and surgeons will be blinded in terms of allocation to individual arms (until the envelope is opened). Unblinding will take place at the end of the trial via phone call (or ambulatory visit if one will be scheduled) by Study Secretary.

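### The Yates/Fisher rule for categorical variables is conservative for uncommon complications; an unconditional exact test at the same 5% level would recover about 6 to 10 points of power

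*Protocol article*

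**What the plan says.** The section on statistical methods for primary and secondary outcomes {20a} sets one rule for every categorical variable: "Chi-square tests of independence will be used for categorical variables (using Yates correction for cell counts below 10", followed by a check of Cochran's conditions and by Fisher's exact test. It does not say whether the cell counts are observed or expected, or at what point Fisher's test takes over. On the level it says that "0.05 will be assumed as the significance level in all calculations".

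The complications are defined under Secondary outcomes: "Incidence of other complications (seroma, hematoma, infections) assessed during hospital stay, 7 days post-op, 3 months, and 12-months after surgery". No separate analysis is named for them, so the generic rule applies. The article gives no expected complication rate, no target difference and no power for them. Its assumed event rate ("Recurrence rate was assumed to be 4% based on literature data"), its 8% threshold and its 80% power all belong to recurrence.

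On size, "sample size was established at 204 participants", with randomization "on 1:1 basis by Study Secretary" and the statement that "A percentage loss of 10% was assumed".

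**The concern.** Yates' correction and Fisher's exact test are conservative when events are few. With about 92 to 102 patients per arm, a cut-off of 10 sends almost every uncommon complication to one of them. A comparison planned at 5% is then in practice made at a much stricter level.

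The Discussion argues that avoiding fixation removes several risks, infection among them. The complication comparison is where such a benefit, or a harm of the unfixed mesh, would show. Apart from frequencies and percentages, the significance test is the only between-arm inference the section names for these outcomes. A conservative test makes a report of no significant difference more likely than it need be.

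**Working it through.** **Plan's own figures.** For complications the article states only the nominal 0.05. Its computed figure, 83–102 per arm, is for recurrence. The lower end reproduces: 4% in both arms, margin 8%, one-sided 5% and 80% power give 75 per arm, and 75 × 1.1 = 82.5, so 83. It says nothing about harms.

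**Inputs.**
- Randomized per arm: 204 / 2 = 102.
- Evaluable after 10% loss: 102 × 0.9 = 91.8, taken as n = 92.
- Level 0.05, taken as two-sided.
- Complication incidences: assumptions throughout, shown as a range.

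**The rule as read.** Fisher if the smallest expected count is below 5; otherwise Yates if any observed cell is below 10; otherwise plain Pearson. If Fisher is triggered by an observed cell below 5 instead, the size at 10% incidence and 92 per arm is 2.8% rather than 2.5%, so the unclear wording matters little.

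**Formulas.** Let x and y be the events per arm, N = 2n and t = x + y.
- Pearson: N(x − y)² / [t(N − t)]
- Yates: N(|x − y| − 1)² / [t(N − t)]
- N−1: (N − 1)(x − y)² / [t(N − t)]
- Boschloo: reject when Fisher's p is at or below the largest cut-off that keeps the maximum size over all common rates at 5% or less. The cut-off is 0.0677 at 92 per arm (maximum size 4.99%) and 0.0650 at 102 (4.91%).
- Size or power: the sum over all (x, y) of Bin(x; n, p₁) × Bin(y; n, p₂) × [test rejects].

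**One table by hand: 2 v 9 events, n = 92.** Here t = 11, N − t = 173 and t(N − t) = 1903. The smallest expected count is 11 / 2 = 5.5, so Yates applies: 184 × 6² / 1903 = 3.48, p = 0.062. N−1 gives 183 × 7² / 1903 = 4.71, p = 0.030. Boschloo also rejects, since Fisher's p of 0.058 is below 0.0677. The tables 0 v 5, 1 v 7 and 3 v 11 behave the same way: not significant under the rule, significant under both alternatives.

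**How often the cut-off of 10 bites (92 per arm).** The chance that at least one arm has fewer than 10 events is over 99% at 4% or 6% incidence, 96% at 8%, 81% at 10%, 19% at 15% and 1% at 20%.

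**True two-sided size, 92 per arm (%).**

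| Incidence | Rule | Boschloo | N−1 |
|---|---|---|---|
| 2% | 0.36 | 1.33 | 3.69 |
| 4% | 1.47 | 3.25 | 4.29 |
| 6% | 1.95 | 3.66 | 4.45 |
| 8% | 2.20 | 3.86 | 4.94 |
| 10% | 2.52 | 4.02 | 5.10 |
| 15% | 3.74 | 4.26 | 4.93 |
| 20% | 4.81 | 4.50 | 4.94 |

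Over all common rates, N−1 peaks at 5.1% (92 per arm) and 5.4% (102 per arm).

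**Power (%): rule / Boschloo / N−1.** Losses are taken before rounding.

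| Contrast | 92 per arm | Loss v Boschloo, v N−1 | 102 per arm | Loss v Boschloo, v N−1 |
|---|---|---|---|---|
| 2 v 10% | 51.5 / 61.8 / 64.5 | 10.3, 13.0 | 57.7 / 66.3 / 70.2 | 8.6, 12.5 |
| 3 v 12% | 53.4 / 62.7 / 66.5 | 9.4, 13.1 | 59.6 / 66.2 / 72.0 | 6.6, 12.4 |
| 4 v 14% | 56.5 / 64.9 / 68.9 | 8.4, 12.4 | 62.5 / 68.4 / 73.9 | 5.8, 11.4 |
| 5 v 15% | 52.5 / 60.3 / 64.3 | 7.8, 11.8 | 58.0 / 64.1 / 69.2 | 6.1, 11.2 |
| 8 v 20% | 59.9 / 63.7 / 66.4 | 3.8, 6.5 | 66.1 / 67.8 / 71.4 | 1.8, 5.3 |
| 10 v 20% | 42.9 / 45.4 / 47.9 | 2.5, 5.0 | 48.8 / 48.9 / 52.4 | 0.1, 3.6 |

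The extremes lie on both sides. At 1 v 5% with 92 per arm the loss against N−1 is 18.3 points. At 10 v 25% with 102 per arm Boschloo is 0.9 points less powerful than the written rule.

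**The case against.** - **The tests are valid.** Yates and Fisher are standard, and 0.05 is a nominal ceiling. A reader might infer that a true error of 0.4% to 2.5% contradicts the stated 5%. It does not: the article never promises that the attained size equals 5%, and a test that stays below its level respects it. This stands.
- **The rule is generic.** A reader might take it as designed for the complications. The text names all categorical variables alike, and the complications merely fall under it. This stands.
- **Every rate is assumed.** If a complication such as seroma ran at 15% to 20%, the rule's size would be 3.7% to 4.8% and little would be lost. This stands, so the size of the effect can only be given conditionally.
- **The choice of comparator matters.** N−1 can exceed 5%, which flatters the gain. This stands in part: against Boschloo, which holds 5%, most of the gain on the sparse contrasts remains.
- **Little may change in practice.** Even the alternatives reach only 60% to 69% power on the four sparse contrasts at 92 per arm. Three complications are assessed at four times with no multiplicity adjustment described, so a less conservative test will give more false positives over the set. Table 1 also ranks complications as other outcomes. These are reasons to rate the point low, not to keep an avoidable loss.
- **The article is condensed.** Interval methods for secondary outcomes may sit in an unseen analysis plan, so their absence is no fault here. The test rule itself is written out and can be judged as it stands.

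**Conclusion.** The point holds as an inexpensive efficiency improvement on secondary outcomes. The plan contains no error here. At 92 evaluable per arm and assumed incidences of 2% to 10%, the written rule runs at about 0.4% to 2.5% two-sided. On assumed contrasts from 2 v 10% to 5 v 15% it gives up about 8 to 10 points of power against a test that holds 5% (about 6 to 9 points at 102 per arm), and about 12 to 13 points against N−1. At 8 v 20% and 10 v 20% the loss at 92 per arm is 6.5 and 5.0 points against N−1, and under 4 points against Boschloo.

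Two wider readings are not supported. The loss is not a general property of the rule, because it depends on rates the article does not give. Nor does any of this bear on the primary outcome: recurrence is a non-inferiority question, and these calculations concern tests of difference for complications.

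**What to change.** In {20a}, exempt the binary complication outcomes from the Yates clause. Suggested wording: *Seroma, hematoma and infection will each be compared between arms with a two-sided unconditional exact (Boschloo) test at 0.05, and the risk difference will be reported with a score (Miettinen–Nurminen) 95% confidence interval.* The N−1 chi-square is an acceptable alternative where expected counts allow. Whichever is chosen, name it, with any expected-count cut-off, before the data are seen.

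The cost is one sentence and no extra data. N−1 may slightly exceed 5%; Boschloo does not, but for commoner events it gains nothing or may lose about a point. Boschloo's test and score intervals may need software other than STATISTICA 12 or Excel.

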### Trial design {8}

MEFI Trial is a prospective, non-inferiority, parallel, two-armed, multicenter, double-blinded randomized controlled trial to study outcomes of non-fixation of the mesh in terms of recurrence in large M3 defects during laparoendoscopic hernia repair techniques. Eleven large surgery centers in Poland, proficient in laparoendoscopic groin hernia repairs (performing at least 80 TAPP/TEP procedures a year), were selected for this study (Table 1 and Fig. 1). List of study sites (collaborators) is given in the Organizational Structure and Responsibilities section at the end of document. Recurrence rate in 12-month follow-up was set as a primary outcome.

**Table 1 Tab1:** Schedule of enrolment, interventions, and assessments for the MEFI trial

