#### Primary outcome

The primary endpoint is the recurrence rate in 1-year follow-up.

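### The only test stated for a binary outcome such as recurrence has a no-difference null and is not linked to the 8% margin, so the stated analysis cannot answer the non-inferiority question

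*Protocol article*

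**What the plan says.** - **Design.** Protocol article, Trial design {8}: "MEFI Trial is a prospective, non-inferiority, parallel, two-armed, multicenter, double-blinded randomized controlled trial". Objectives {7} puts the non-inferiority hypothesis in terms of recurrence.
- **Endpoint.** Primary outcome: "The primary endpoint is the recurrence rate in 1-year follow-up". Each patient either has a recurrence or does not, so the variable is binary.
- **Sizing.** Sample size {14}, repeated in the second paragraph of {20a}: "The trial was planned as non-inferiority study with test power = 80" per cent, a p-value of 0.05, "threshold for clinical significance = 8" per cent, "Recurrence rate was assumed to be 4% based on literature data" and "A percentage loss of 10% was assumed". The result is 83–102 per arm, and 204 patients in total.
- **Analysis.** The first paragraph of {20a}, whose heading covers primary and secondary outcomes, is organised by type of variable. For categorical variables: "Chi-square tests of independence will be used for categorical variables", with the Yates correction when cell counts are below 10 and Fisher's exact test as needed. The level is fixed for everything: "0.05 will be assumed as the significance level in all calculations". A 95% confidence interval is listed for continuous variables; qualitative variables get frequencies and percentages.
- **Anything further.** Section {20b} rules out additional analyses.

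**The concern.** Chi-square, Yates and Fisher tests all take equal recurrence in the two arms as the null hypothesis. A non-inferiority claim needs the opposite arrangement: the null is that non-fixation is worse by at least the margin, and the data must reject it. Failing to reject equality is not evidence that the excess is below 8 points. In a trial of this size with few events it is the likely result over a wide range of true differences, and the small-count corrections make it likelier still.

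Taken literally, then, the stated analysis leaves the primary hypothesis untested. The 8% threshold sets the sample size, but no result is ever compared with it. If someone filled the gap by treating p > 0.05 as success, the false-claim rate would not be controlled. The claim at stake is the one the Background and Discussion sections want to use to change international guidelines.

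**Working it through.** **Inputs.** From {14} and {20a}: recurrence 4% (taken as true in both arms), margin 8% (read as an absolute difference), power 80%, alpha 0.05 with no sidedness stated, loss 10%, total 204. From {16a}: 1:1 allocation, so 102 per arm. After 10% loss: 102 × 0.9 = 91.8, about 92 evaluable per arm.

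**Step 1: reproduce the planned size.** Non-inferiority for two proportions, unpooled variance:

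n = (z_α + z_β)² × 2p(1 − p) / δ², with 2 × 0.04 × 0.96 / 0.08² = 0.0768 / 0.0064 = 12.

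- One-sided 0.05: (1.645 + 0.842)² × 12 = 74.2, so 75 per arm. With loss: 75 × 1.1 = 82.5, so 83. This is the lower stated figure.
- One-sided 0.025: (1.960 + 0.842)² × 12 = 94.2, so 95 per arm. With loss: 95 × 1.1 = 104.5, so 105, within 3% of the upper stated figure of 102 (95 / 0.9 gives 106).

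For comparison, a two-sided 0.05 difference test of 4% against 12% with 80% power (average rate 8%):

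n = [1.960 × √(2 × 0.08 × 0.92) + 0.842 × √(0.04 × 0.96 + 0.12 × 0.88)]² / 0.08² = 179.3, so 180 per arm before loss.

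The planned size is therefore a non-inferiority calculation. It is too small for the test that {20a} states.

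**Step 2: how often the stated test is non-significant.** Exact enumeration of two independent binomials, 92 per arm, adding the probability of every table with two-sided p ≥ 0.05:

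| True rates (control vs non-fixation) | Fisher | Yates | Uncorrected chi-square |
|---|---|---|---|
| 4% vs 12% (at the margin) | 0.576 | 0.603 | 0.470 |
| 4% vs 14% | 0.412 | 0.435 | 0.311 |
| 4% vs 16% | 0.271 | 0.285 | 0.189 |

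The control arm expects 92 × 0.04 ≈ 4 recurrences, so the protocol's rule for cell counts below 10 leads to the Yates or Fisher columns. At 4% vs 12%, going from 83 to 102 evaluable per arm moves Fisher from 0.621 to 0.525, Yates from 0.654 to 0.550 and uncorrected chi-square from 0.522 to 0.418.

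**Step 3: a test that uses the margin.** Same enumeration, 92 per arm, declaring non-inferiority when the upper Newcombe limit for the difference (non-fixation minus fixation) is below 8 points:

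| True rates | One-sided 0.025 | One-sided 0.05 |
|---|---|---|
| 4% vs 12% (false claim) | 0.023 | 0.048 |
| 4% vs 4% (power) | 0.673 | 0.809 |

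Farrington–Manning gives the same values to three decimals. A simple Wald limit gives power of 0.791 and 0.873, but false-claim rates of 0.037 and 0.063, above nominal.

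**Step 4: one table.** 4/92 (4.3%) on fixation and 12/92 (13.0%) on non-fixation, a difference of 8/92 = 8.7 points. Fisher p = 0.064 and Yates p = 0.067, so no significant difference under the protocol's small-count rule. Uncorrected chi-square gives p = 0.036. The 95% Newcombe interval is 0.4 to 17.5 points: its upper limit is more than twice the margin and its lower limit is above zero. The protocol's own choice of test decides whether this table reads as no difference.

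**The case against.** The strongest reply is that the first paragraph of {20a} is a generic list, sorted by variable type, that never names recurrence. The paragraph after it, under the same heading, restates the non-inferiority plan with its 8% threshold and mentions a primary analysis without describing it. This is a journal article, a full protocol exists, and an analysis plan may exist too; the choice of interval method is often left to those documents.

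Part of this stands. The lack of a named interval method would not be a finding by itself, and it would be wrong to say that {20a} never mentions the 8%. But the article is not silent on analysis. Under a heading that covers the primary outcome it states a test for categorical variables, applies 0.05 to all calculations, and {20b} excludes anything further. A margin-based analysis elsewhere would have to depart from that text.

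Two stronger readings are tempting and go too far:

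- **That the trial will declare non-inferiority when p > 0.05.** No section says so. The text points that way only because it offers no other route to its conclusion, and because the abstract and Discussion speak of equal recurrence in the two groups.
- **That a clearly inferior arm would pass more than half the time.** The figure above one half belongs to 12% against 4%, which lies on the margin and not beyond it, and to the Fisher and Yates versions. It is already 47% with uncorrected chi-square, and with Fisher or Yates it falls to 41–44% at 14% and 27–29% at 16%.

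**Conclusion.** The concern holds in this form: the only inferential method stated for a binary outcome tests a null of no difference, and the 8% threshold is connected to no test, interval or decision rule. The stated analysis therefore cannot answer the non-inferiority question. This is a wrong method in the text, not a missing detail, and it bears on the trial's main claim, so it should be corrected before analysis. That conclusion needs no numerical assumption.

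The size of the risk is conditional. Suppose non-significance were taken as non-inferiority, the true rates were 12% and 4%, 92 patients per arm were evaluable, and the prescribed small-count tests were used. The arm at the margin would then pass about 58–60% of the time, against about 2–5% under a Newcombe test of the 8-point margin. The comparison also assumes that 8% is an absolute difference, which the 83 per arm supports.

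**What to change.** In {20a}, state that:

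1. The primary analysis is the difference in 12-month recurrence proportion, non-fixation minus fixation, with a score-type confidence interval such as Newcombe or Farrington–Manning. The choice between the two is a matter of preference.
2. Non-inferiority is concluded only if the upper limit is below 8 percentage points.
3. The one-sided alpha is a named value. One-sided 0.05 matches the lower stated size of 83 per arm and gives about 81% power at 92 evaluable per arm. If one-sided 0.025 is chosen, the stated 80% should be restated as about 67% with a score-type interval.
4. Chi-square, Yates and Fisher tests are kept for baseline and secondary variables, and a non-significant difference test is not evidence of non-inferiority.

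The cost is protocol wording, plus a less favourable stated power if one-sided 0.025 is chosen. No new data items are needed.
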